##### Subjects’ timeline

One day before a given subject’s laparoscopic surgery, the investigators will decide whether to include them in the trial. This will be considered day 0 of the experiment. The subjects will receive their first postoperative intervention 6 h after surgery. Thereafter, interventions will be repeated every 12 h until a total of six interventions have taken place. The first evaluation will occur on day 0. Evaluations will then take place after each intervention, for a total of seven evaluations. For an overview of the recruitment timeline, interventions, and subject assessment, see Fig. 2.

### Data collection

For reasons of convenience, we will consolidate all subjects’ scores, observation times, adverse event records, and safety assessments into a single case report form (CRF). We will require the researchers to fill out the CRFs immediately and accurately.

### Quality control

#### Quality control system

We will establish a two-level quality assurance system. The first level will consist of quality inspection. For this purpose, the project leader (PL) will appoint a quality inspector, who will check the original data records, data reports, and adverse event logs using a quality assurance list. This person will also investigate any possible violations of protocol. The PL will immediately select an appropriate course of action if any quality problems arise. The second level will consist of quality monitoring. The clinical research monitor will monitor the medical practitioners to ensure they have an appropriate understanding of the research program, check that the processes are being correctly implemented, and ensure that all research data, reports, and CRFs are true, accurate, complete, and consistent with the actual data.

#### Quality control specifications

1) We will analyze potential confounding factors to decrease bias in the research results. 2) We will strictly execute the trial protocol and adhere to the standards of the treatment methods. 3) All investigators are certified doctors or nurses with professional acupuncture training. 4) We will strictly implement the randomization program that assigns subjects to two groups. 5) Researchers familiar with the scales will design the protocol regarding scoring methods, evaluation times, and evaluation forms. They will also standardize the way in which questions relate to the scales. The evaluators will adhere strictly to these principles when carrying out clinical evaluations. 6) The investigators will closely observe the included subjects and fill out the CRFs in accordance with the instructions. The data must be recorded diligently and completely. After attaching the data inspection report, no investigator will be permitted to change the original data. If any change is made, a detailed explanation must be provided and signed by the modifier. 7) The devices to be used in the trial will be purchased in one batch for consistency and reliability of data collection and research outcomes. 8) Subject compliance will be ensured.

### Sample size estimation and statistical analysis

#### Sample size estimation

The trial will test two groups in parallel. The following formula was used to estimate the required sample size:$$ n=\frac{{\left({Z}_{1-\alpha /2}+{Z}_{1-\beta}\right)}^2\kern0.5em \times \kern0.5em \left({\sigma}_1^2+{\sigma}_2^2\right)}{\delta^2} $$

In this formula, *n* is the number of samples in each group, σ is the standard deviation, and δ represents the difference with clinical significance between two groups. Using the parameters *α* = 0.05 and power = 80%, the corresponding Z values for a bilateral test are Z_1–α/2_ = 1.96, Z_1–β_ = 0.84. In the November 2016 pilot trial, the average times until the first postoperative flatus in the XN and SH groups were S_1_ = 2.89 h and S_2_ = 4.31 h, respectively. Based on this clinical experience, we defined 4 h as a clinically significant difference in time until first postoperative flatus between the two groups. By substituting these values into the formula above, we obtained the parameter *n* = 13.19. Rounding up to the next whole number, the number of samples in each group should be 14. Assuming a loss rate of 15%, the final number of samples in each group will be 17. Hence, the total number of subjects in the present study will be 34.

#### Statistical analysis

##### Analysis procedures

*Sample distribution:* We will describe the size and dropout rate of each dataset. Detailed reasons for any dropouts will be provided.

*Balanced comparison:* We will compare the general subject data and then evaluate comparability between the two groups.

*Efficacy analysis:* We will use the time until the first postoperative flatus as a primary outcome to assess the efficacy of XNKQAT by intradermal needling in the treatment of gastrointestinal dysfunction after laparoscopic surgery. We will calculate the average and standard deviation to describe the outcome and use an independent-samples *t* test to compare the two groups. Eight secondary outcomes (time until first postoperative defecation; level of abdominal pain, abdominal distension, and nausea; blood ghrelin level; vomiting; psychological status; and quality of life) will be compared between the two groups to determine the efficacy of XNKQAT intradermal needling. The mean and standard deviations of these parameters will be reported. To record the subjects’ psychological status, we will record their scores and determine their classification based on the standards mentioned above. To determine the time until the first postoperative defecation, we will use the same method as the time until the first postoperative flatus. To analyze abdominal pain, abdominal distension, nausea, vomiting, ghrelin level, and quality of life, we will use repeated measures analysis of variance (RMANOVA). Before RMANOVA, we will carry out a test of sphericity to ensure that the data are suitable for this method. If the data do not meet spherical symmetry requirements, we will use the ε correction factor to correct the degrees of freedom before applying RMANOVA. The Mann–Whitney *U* test or Spearman’s Rank correlation coefficient tests will be used to analyze the categorization standards for psychological status.

*Safety analysis:* According to the definition of adverse events, specific adverse events will be listed, along with their severity level, causes, and explanations. The number of adverse events, and the adverse event rate, will be described statistically. If they need to be compared between groups, the χ^2^ test or Fisher’s exact test will be used.

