### Study subjects

The study will recruit inpatients of the Department of Minimally Invasive Surgery, Tianjin Nankai Hospital, Tianjin, China, who are scheduled to undergo laparoscopic surgery between March and November 2017. Based on the six-subject pilot trial described above, which was performed in November 2016, the present trial will compare the time until first postoperative flatus between the two groups; we consider this the primary outcome in the recovery of gastrointestinal function. In addition, the pilot trial’s intervention was based on that of the present formal trial. The treatment in the pilot trial was needling (or sham needling) at PC6 on both forearms, SP6 on both ankles, and DU26; that is, at a total of five acupoints. Using the parameters α = 0.05 and power = 80%, and assuming a dropout rate of 15%, 34 participants will be required to participate in the full-scale study to ensure statistically meaningful results.

To ensure that the results are accurate, the present study will include strict inclusion, exclusion, and elimination criteria, as outlined below.

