#### Inclusion criteria

To enroll in the trial, subjects must: 1) be aged 18–65 years; 2) be scheduled to undergo elective laparoscopic surgery under general anesthesia; 3) have no experience with intradermal needling therapy; 4) not be enrolled in any other clinical trials; 5) have no cognitive dysfunction, aphasia, mental illness, or other communication barriers; and 6) be able to sign an informed consent form.

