### Randomization

Patients will be assigned in a 1:1 ratio to either the XN group or the SH group using random numbers generated in SPSS 19.0. To reduce selection bias and avoid other confounding factors, a specifically appointed investigator will be in charge of the randomization process. When recruiters identify a subject who meets the criteria for participation, they will obtain a sequence number for that subject from the researcher in charge of the randomization process.

To prevent the biases of the researchers from influencing the authenticity of the clinical findings, the subjects’ group allocations will be concealed from the recruiters and evaluators using the sealed envelope method. Briefly, the subjects’ allocation will be concealed inside sealed, opaque, serialized envelopes from the researchers responsible for recruitment and treatment evaluation. To ensure strict confidentiality, the envelopes will not be transparent, even under intense light. To prevent confusion around the group assignments, the subjects’ full names and birthdates will be written on the outside of their envelopes using carbon paper. The information on the sealed envelopes, and the details about the subjects, will be video-recorded, and the carbon copy of the label on the outside of the sealed envelope will then be attached to the group allocation card inside the envelope. Next, another researcher will check the videos to ensure the subjects’ envelopes are sealed. The entire process of opening the envelopes will also be video-recorded. The envelopes will be opened, and the assigned intervention type (XNKQAT or sham) will only be known after the respective subject has undergone all baseline evaluations.

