### Outcome measures and subjects’ timelines

#### Outcome measures

##### Baseline information

Demographic information will be collected using a custom-made, standardized survey form that includes age, gender, educational background, occupation, weight, and height.

Surgical procedure information will be collected using a custom-made, form that collects information regarding clinical characteristics, including surgery and anesthesia duration, blood loss during surgery, infusion volume during surgery, and vital signs during surgery (body temperature, cardiac rate, breathing rate, and blood pressure).

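### The primary t test is unadjusted and the promised confounder analysis is undefined; prespecifying one surgical covariate would close the choice and may gain precision

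*Protocol article*

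**What the plan says.** All references are to the protocol article.

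- **Primary test.** Under Analysis procedures, the plan for time to first flatus is to "use an independent-samples *t* test to compare the two groups". No covariate is named.
- **Use of baseline data.** The same section says: "We will compare the general subject data and then evaluate comparability between the two groups". It gives the baseline data no further role.
- **Confounders.** Quality control specifications, item 1, says: "We will analyze potential confounding factors to decrease bias in the research results". It does not say which factors, for which outcome, or by what method.
- **Population.** The surgical inclusion criterion is to "be scheduled to undergo elective laparoscopic surgery under general anesthesia". The exclusion criteria do not restrict the type of laparoscopic procedure.
- **Data collected.** Under Baseline information, the surgical form records clinical characteristics, "including surgery and anesthesia duration, blood loss during surgery, infusion volume during surgery, and vital signs during surgery".
- **Timing.** The Intervention section puts the first treatment 6 h after surgery.
- **Allocation.** Under Randomization: "Patients will be assigned in a 1:1 ratio to either the XN group or the SH group using random numbers generated in SPSS 19.0". No stratification is described.

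**The concern.** A mixed set of laparoscopic operations can be expected to differ in extent, and extent of surgery may plausibly predict the return of bowel function. Neither the allocation nor the analysis, as described, uses that information, although a usable measure of it is already on the form. Surgery and anaesthesia duration are complete before any needling, so treatment cannot affect them and they are legitimate covariates.

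Two things are at stake. The first is efficiency. In a trial of 34 subjects, variance that a recorded covariate could explain stays in the error term of the t test. The second is prespecification. The analysis section fixes an unadjusted test, while the quality control section promises to deal with confounders. The two statements are not connected, so whether to adjust, and for what, could be decided once the baseline table and the outcome are known.

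**Working it through.** **Inputs.** From Sample size estimation: two-sided α = 0.05, power 80%, difference 4 h, 15% loss. The SDs are 2.89 h and 4.31 h. That section calls them average times, but the Background shows that they are the pilot SDs. The share of outcome variance explained by duration (R²) is not in the document; it is an assumption, shown from 0 to 0.30.

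**The plan's own figure.** n = (1.96 + 0.84)² × (2.89² + 4.31²) / 4² = 7.84 × 26.93 / 16 = 13.19, rounded up to 14 per arm. 14 / 0.85 = 16.5, rounded up to 17 per arm, 34 in total. This reproduces exactly. It is a calculation for the unadjusted comparison.

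**Unadjusted power.** Root-mean-square SD = √(26.93 / 2) = 3.67 h. SE = 3.67 × √(2/n), which is 1.387 h at 14 per arm and 1.259 h at 17. Noncentrality = 4 / SE = 2.884 and 3.178. The noncentral t with 2n − 2 degrees of freedom (26 and 32) gives 79.3% and 86.9%.

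**Adjusted power, one covariate.** The SE is multiplied by √[(1 − R²) × (1 + 1/(2n − 4))] and the degrees of freedom fall to 2n − 3. The second factor is the expected cost of chance imbalance in the covariate: 1 + 1/24 = 1.042 at 14 per arm and 1 + 1/30 = 1.033 at 17.

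| R² (assumed) | SE ratio, 14 / 17 per arm | Power at 14 per arm | Power at 17 per arm |
|---|---|---|---|
| t test, no covariate | 1 | 79.3% | 86.9% |
| 0 | 1.021 / 1.017 | 77.5% | 85.7% |
| 0.10 | 0.968 / 0.964 | 81.7% | 89.1% |
| 0.20 | 0.913 / 0.909 | 85.9% | 92.3% |
| 0.30 | 0.854 / 0.850 | 90.1% | 95.1% |

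**Break-even.** The SE is unchanged when (1 − R²) × inflation = 1. That is R² = 1 − 1/1.042 = 0.04 at 14 per arm and 1 − 1/1.033 = 0.03 at 17.

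**If the pilot SD is too small.** The pilot had six patients, so its SDs are very uncertain. With an SD of 5 h (assumption), power at 17 per arm is 62% unadjusted, 60% at R² = 0, 65% at 0.10, 70% at 0.20 and 76% at 0.30. The pattern is the same: a small loss if the covariate is useless, a larger gain if it is moderately prognostic.

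**Chance imbalance.** The SD of the shift in the treatment difference due to imbalance in duration is 3.67 × √R² × √(2/n). For R² of 0.20 to 0.30 this is 0.62 to 0.76 h at 14 per arm and 0.56 to 0.69 h at 17.

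**The case against.** The strongest reply is that nothing here is wrong. With 1:1 randomization the unadjusted t test is valid, chance imbalance is already reflected in its standard error, and the test matches the sample size formula. Covariate adjustment is often left to a statistical analysis plan, which is not shown. The gain depends on an R² that the article does not give, and at 17 per arm the unadjusted test already has 87% power at the pilot SDs. All of this stands, and it limits the point to efficiency and prespecification. It does not remove the point, because the article itself names the unadjusted test and separately promises a confounder analysis without connecting the two.

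A reader might infer more than the document supports:

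- **That imbalance in long operations could create or hide a 4 h difference.** It could not realistically do so at the pilot SDs. With a shift SD of 0.56 to 0.76 h, 4 h is 5.3 to 7.1 SDs away.
- **That covariates will be selected by balance tests.** No section says so. The text speaks only of comparing the data and judging comparability.
- **That type of operation is missing from the surgical form.** The list of fields is introduced as examples and the form is not shown, so this is not established.
- **That the article shows extent of surgery to vary widely or to drive recovery.** It does not. It shows only that eligibility is not limited by procedure.

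One further doubt does not matter here. The Subjects' timeline section places the first evaluation on day 0, the day before surgery, whereas other sections place it 6 h after surgery, so the time at which the envelope is opened is unclear. On either reading, duration is fixed before the first treatment.

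**Conclusion.** The point holds as a recommended improvement, not as an error. The stated primary test is valid and the stated sample size is correct for it. What is weak is that a recorded, pre-treatment and plausibly prognostic variable is left out of the primary comparison, while a general promise about confounders leaves later adjustment open.

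The size is modest and conditional. For R² between 0.10 and 0.30, the gain is about 2 to 11 points of power at 14 per arm and about 2 to 8 points at 17. The loss is 1 to 2 points if duration is not prognostic. These figures assume the six-patient pilot SDs, a 4 h difference, a linear covariate effect and approximately normal errors. The R² range is an assumption throughout.

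**What to change.** Add to the efficacy analysis: the primary comparison of time to first flatus is a linear model with treatment arm and one covariate, anaesthesia duration (or surgery duration; choose one now), with the unadjusted t test reported beside it. State that this is the confounder analysis meant in item 1 of Quality control specifications, and that the comparability table is descriptive. Fix the wording before unblinding.

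One covariate is enough at this size. A second raises the break-even R² to about 0.06 to 0.08.

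The cost is a sentence or two of text and one degree of freedom. No extra subjects or data are needed, and the sample size of 34 can stay as it is.

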**Fig. 2 Fig2:**
[figure not shown]
The schedule of enrollment, interventions, and assessments. *-t*
_*1*_ the day before the surgery, *t*
_*0*_ the day of the surgery, *t*
_*1*_
*-t*
_*6*_ the days in hospital after the surgery, *t*
_*7*_ the day of the discharged, *t*
_*8*_ 14 days after the discharged, *t*
_*9*_ 30 days after the discharge, *SH* sham, *XN Xingnao Kaiqiao* acupuncture technique

Using random numbers generated in SPSS 19.0, we will allocate subjects to either the XN group or the SH group at a ratio of 1:1. To reduce selection bias, a specifically appointed investigator will be in charge of the random allocation and other confounding factors. The first XNKQAT treatment will take place 6 h after surgery and will be followed by another treatment every 12 h thereafter until a total of six treatments have been completed. Each treatment will last 3 min. The patients will subsequently attend three follow-up visits. In addition, seven evaluations will be performed to monitor outcomes related to the recovery of gastrointestinal function. The first such evaluation will take place immediately before the first treatment, 6 h after surgery. The evaluations will be repeated every 12 h thereafter until a total of seven evaluations have been completed.

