##### Secondary outcomes

*First postoperative defecation:* The time until the first postoperative defecation will be recorded, beginning at the time when the subject returns to the ward after surgery. The subjects and their family members will be instructed to record the time of the first postoperative defecation:

Time of the first postoperative defecation = the moment of the first postoperative defecation – the moment when the subject returned to the ward after surgery

*Abdominal pain:* A VAS will be used to estimate the level of the subjects’ postoperative abdominal pain [21]. The first assessment will be performed 6 h after the laparoscopic surgery, ahead of the first treatment. Thereafter, pain will be assessed every 12 h until a total of seven evaluations have been performed. The subjects and their families will assist in keeping the abdominal pain record.

*Abdominal distension:* A Likert scale will be used to evaluate the subjects’ abdominal distention after surgery [22]. The first assessment will be performed 6 h after laparoscopic surgery, ahead of the first treatment. Thereafter, distention will be assessed every 12 h until a total of seven evaluations have been performed. The subjects and their families will assist in keeping the abdominal distension record.

*Nausea:* A VAS scale will be used to evaluate the level of the subjects’ nausea [21]. The first assessment will be performed 6 h after laparoscopic surgery, ahead of the first treatment. Thereafter, nausea will be assessed every 12 h until a total of seven evaluations have been performed. The subjects and their families will assist in keeping the nausea record.

*Vomiting:* We will evaluate the number of times the subject vomits after surgery. The first assessment will be conducted 6 h after laparoscopic surgery, ahead of the first treatment. Thereafter, assessments will be performed every 12 h until a total of seven evaluations have been performed. The subjects and their families will assist in keeping the vomiting record.

*Ghrelin test:* Blood will be drawn for ghrelin testing once before surgery and again before discharge from the hospital. A total of 3 mL of blood will be collected from a vein in the morning, when the subject has an empty stomach. The blood sample will be allowed to sit for 30 min at room temperature and then be centrifuged at 3500 rpm for 10 min. The supernatant will be cryopreserved for ghrelin testing.

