#### Statistical analysis methods

The data will be analyzed according to the intention-to-treat (ITT) principle; that is, all subjects who are initially included in one of the two groups will be considered in the analysis. The analysis of efficacy and safety indicators will be carried out per-protocol (PP) and will include all subjects who complete the whole trial process. The quantitative variables of the research data will be statistically described using $$ \overline{\mathrm{X}}\kern0.5em \pm \kern0.5em \mathrm{SD} $$. A record of qualitative variables will be kept using the number of cases in each category. To compare quantitative variables, if the data come from repeated measurements, the RMANOVA method will be used, and sphericity testing will be used beforehand to determine whether a correction is needed. Qualitative data will be analyzed using the Mann–Whitney *U* test or Spearman’s rank correlation. The χ^2^ test or Fisher’s exact test will be used to compare the occurrence rates of countable data. Statistical testing will be two-tailed, with *P* values < 0.05 considered significant. SPSS 19.0 software will be used for all statistical calculations.

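### Six secondary outcomes go to repeated-measures ANOVA with no baseline covariate, no named between-group test and a need for complete readings, so pre-treatment values are used poorly and the analysis set is left in conflict

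*Protocol article*

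**What the plan says.** Under Analysis procedures, the protocol article states: "To analyze abdominal pain, abdominal distension, nausea, vomiting, ghrelin level, and quality of life, we will use repeated measures analysis of variance (RMANOVA"). A sphericity test comes first, with an epsilon correction of the degrees of freedom if it fails. Statistical analysis methods repeats this for repeated quantitative data. Neither section names a baseline covariate, or says whether the group term or the group-by-time term is the comparison of the arms.

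The readings are these:

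- **Pain, distension, nausea and vomiting:** seven each, 12 h apart. The Design section says of the first: "The first such evaluation will take place immediately before the first treatment, 6 h after surgery". Secondary outcomes agrees.
- **GIQLI:** three, at 6 h after surgery, at discharge and 1 month after discharge.
- **Ghrelin:** two, before surgery and before discharge.

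Vomiting is defined as a count: "We will evaluate the number of times the subject vomits after surgery".

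On the analysis set, Statistical analysis methods first commits to intention-to-treat for everyone allocated. It then says that efficacy and safety are analysed per-protocol in subjects who finish the whole trial.

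On timing, Subjects' timeline makes the day before surgery day 0 and adds: "The first evaluation will occur on day 0. Evaluations will then take place after each intervention, for a total of seven evaluations".

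**The concern.** Before treatment, randomised arms can differ only by chance. A pre-treatment reading therefore carries no treatment effect, but it predicts the later readings and is best used as a covariate. With no covariate named, the plain reading is that it enters as one more response level. For ghrelin, which has only two values, no other reading is possible. Since the test term is also open, a reader cannot tell what effect will be estimated.

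A sphericity test with an epsilon correction points to the classical form of the method, which uses only subjects with every reading. Together with the completer-only sentence, this puts the secondary comparisons on a selected subset of a 34-subject trial. Six of the eight secondary outcomes are affected.

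**Working it through.** **1. The plan's own figure.** The only computed size is for the primary outcome. The inputs are in Sample size estimation: "we defined 4 h as a clinically significant difference in time until first postoperative flatus between the two groups" and "S_1_ = 2.89 h and S_2_ = 4.31 h".

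n = (1.96 + 0.84)² × (2.89² + 4.31²) / 4² = 7.84 × 26.9282 / 16 = 13.19, rounded up to 14. Then 14 / 0.85 = 16.5, so 17 per group and 34 in total. This reproduces exactly. It says nothing about the repeated-measures outcomes, for which the article gives no SD, correlation or missing rate. Those inputs are assumptions below.

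**2. Dilution, if the group main effect is the test.** The main effect compares averages over all K levels. If the effect is D at the k post-treatment levels and 0 before treatment, the average difference is D × k/K.

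- Symptoms: 6/7 = 0.857, or 14.3% smaller.
- GIQLI: 2/3.
- Ghrelin: 1/2.

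**3. Efficiency for the symptoms.** Assume unit variance, equal correlation r and a constant effect. The information (squared effect over variance, up to a common factor) is:

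- seven-level main effect: (6/7)² / [(1 + 6r)/7]
- mean of the six post-treatment readings, unadjusted: 1 / [(1 + 5r)/6]
- the same mean adjusted for the 6 h reading (ANCOVA): 1 / [(1 + 5r)/6 − r²]

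| r | Seven-level | Six, unadjusted | ANCOVA | ANCOVA / seven-level |
|---|---|---|---|---|
| 0.3 | 1.837 | 2.400 | 3.061 | 1.67 |
| 0.5 | 1.286 | 1.714 | 3.000 | 2.33 |
| 0.7 | 0.989 | 1.333 | 3.846 | 3.89 |

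At r = 0.5, the ratio 2.33 splits into 1.714/1.286 = 1.33 from leaving out the pre-treatment level and 3.000/1.714 = 1.75 from adjusting for it.

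**4. Power under either test.** These are simulated values (4,000 runs) with 17 per group, a constant 0.8 SD effect and two-sided 0.05. Sphericity holds by construction, so no correction is needed.

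| r | Main effect, 7 levels | Group-by-time | ANCOVA |
|---|---|---|---|
| 0.3 | 0.86 | 0.42 | 0.97 |
| 0.5 | 0.73 | 0.59 | 0.97 |
| 0.7 | 0.61 | 0.85 | 0.99 |

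**5. Complete readings.** If each reading is missing independently with probability q, the expected number of complete subjects is 34 × (1 − q)⁷.

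| q | 1% | 2% | 5% | 10% |
|---|---|---|---|---|
| Complete, of 34 | 31.7 | 29.5 | 23.7 | 16.3 |

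The 15% loss allowance is used up at q = 1 − 0.85^(1/7) = 2.3% per reading. If gaps cluster in the same subjects, fewer are lost.

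**6. Vomiting counts.** Repeated-measures ANOVA was run on simulated sparse, overdispersed counts with no true difference (17 per group, seven readings, mean 0.2 or 0.1 episodes per reading). It rejected in 0.033 to 0.038 of runs against a nominal 0.05.

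**7. Timing.** The Abstract, Design, Intervention and Secondary outcomes put evaluation 1 at 6 h after surgery, before the first session. Subjects' timeline puts it on day 0, which it defines as the day before surgery. Evaluations every 12 h from 6 h end at 6 + 6 × 12 = 78 h. Sessions on the same interval end at 6 + 5 × 12 = 66 h. Evaluations 2 to 6 thus fall at the same nominal hours as sessions 2 to 6, while Subjects' timeline places them after each session. The order within those hours is not settled.

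**The case against.** The strongest reply is that the group-by-time term is a natural test when one level precedes treatment. The 6 h reading is then a reference and nothing is attenuated. For ghrelin, that test is a valid comparison of change. This stands. A reader might infer that the plan dilutes every symptom effect to 6/7, but the text names no test, so the dilution and the efficiency ratios hold only for the main effect. What remains is lower power, and a test that is not fixed.

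Other stronger readings also lack support:

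- **Dropped subjects.** A reader might infer a rule that one missing reading removes a subject. No such rule is written; it follows from the classical method. Handling of missing data may be left to a fuller document. The completer-only sentence, however, is in the text and contradicts the intention-to-treat sentence.
- **Early discharge.** A reader might infer that recovered patients leave before 78 h and are lost. No length of stay is given, and the Fig. 2 caption labels t1 to t6 as days in hospital.
- **Vomiting.** A reader might infer false positives or mostly zero counts. The article gives no vomiting data, and the simulation showed no inflation. The mismatch causes neither dilution nor selection. The Abstract speaks of occurrence, and the χ² or Fisher test is already provided for rates.
- **HADS.** A reader might infer that only categories are analysed. Scores are also recorded, and the general rule for repeated quantitative data would cover them.
- **Timeline.** A reader might infer that a near-zero pre-operative symptom value enters the model. The conflict may be only a day-label slip, and no such values are given.

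**Conclusion.** The point holds in conditional form. The article fixes a method for six secondary outcomes without giving the pre-treatment value a role or naming the test. Under a main-effect test, a constant effect is reduced to 6/7, 2/3 or 1/2, depending on the outcome. Under group-by-time there is no dilution, but simulated power was 0.42 to 0.85 against 0.97 to 0.99 with adjustment. These powers, and the ratios 1.7, 2.3 and 3.9, rest on equal correlation and a constant effect; the powers also assume 0.8 SD and complete data from 17 per group. The loss from incomplete readings cannot be sized from the article: about 32 to 16 of 34 subjects would be complete at 1% to 10% independent missingness. The conflict over the analysis set and the conflict over evaluation 1 are in the text and need no assumption. For vomiting the fault is poor fit, not a shown error rate. This should be changed, but it does not threaten the trial's main result: the primary *t* test is untouched.

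**What to change.** - **Symptoms and GIQLI:** analyse the post-treatment readings in all randomised subjects with available data, using a mixed model with arm, time, arm-by-time and the pre-treatment value as covariate. With at most 34 subjects, use a simple covariance structure or a small-sample correction.
- **Ghrelin and HADS score:** use ANCOVA on the single post-treatment value, with the first value as covariate.
- **Test:** name the arm effect that is the comparison for each outcome, for example the average over the post-treatment readings.
- **Analysis set:** state that the comparison in all randomised subjects leads, and give the completer analysis as supportive.
- **Vomiting:** compare occurrence by Fisher's exact test and total episodes by a rank or count method.
- **Timing:** reconcile Subjects' timeline with the Abstract, Design, Intervention and Secondary outcomes on when evaluation 1 occurs and whether later evaluations come before or after the session at the same hour.

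The cost is revised analysis wording, one reconciled paragraph and a little more analysis work. No new data are needed.
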